### Concomitant Treatments

During the study period, the use of any psychotropic medications or other treatments for the target disorder is prohibited in principle, including psychotherapy and neuromodulation therapies (eg, transcranial magnetic stimulation). Medications for the management of treatment-emergent adverse events are permitted. Any concomitant medications or treatments used during the study, including those administered inadvertently, are documented in the case report forms, with details of drug name, dosage, dates of administration, and indication recorded at each visit. Participants who require initiation of prohibited treatments owing to clinical deterioration will be withdrawn from the study and will receive appropriate clinical care.

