### Sample Size Calculation

Study 3 is a pilot RCT designed to assess feasibility and to generate preliminary effect estimates to inform a definitive future trial. Accordingly, the sample size is based on precision estimation rather than formal power calculation. The primary outcome is the response rate at 8 weeks, defined as a reduction of 50% or greater from baseline in the disorder-specific symptom severity score. We adopted a minimal clinically important difference–anchored CI approach, setting a 20-percentage-point absolute difference in response rates as the threshold for clinical importance. With 50 participants per arm within each diagnostic group, the expected 1-sided 80% CI half-width for the between-group difference in response rates is approximately 8 to 12 percentage points (derived from a response rate of 70% for the control group and a range of between-group differences from 0% to 30%), thereby permitting precise estimation of feasibility metrics and preliminary efficacy signals to plan the definitive trial.

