### Plan for Statistical Analysis

All statistical analyses will be performed using SPSS Statistics (version 23; IBM Corp), R (version 4.3 or higher; R Foundation for Statistical Computing), and MATLAB (MathWorks) with the EEGLAB toolbox for EEG data processing. All hypothesis tests will be 2-sided, with a significance level of *α*=.05.

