#### Primary Outcome Analysis

For the response rate at 8 weeks, between-group comparisons will be conducted using chi-square tests, with results reported as risk difference and risk ratio with corresponding 95% CIs. To accommodate the repeated-measures structure of the data (assessments at baseline and at weeks 1, 2, 4, 6, and 8), linear mixed-effects models for repeated measures (MMRM) will be used for continuous outcomes, with fixed effects for treatment group, time, and their interaction; baseline scores will be included as covariates; and random intercepts for participants will be specified to accommodate within-subject correlation. Because study 3 cannot blind participants and the IMT arm involves additional engagement, 2 prespecified sensitivity analyses will probe the robustness of the primary treatment effect to expectation and attention effects: (1) the MMRM and the response-rate models will be refitted with baseline CEQ scores added as covariates; and (2) the analyses will be repeated with adjustment for the Bang Blinding Index to explore whether the estimated treatment effect is attenuated after accounting for residual unblinding. Concordance between the primary (unadjusted) and these expectancy-adjusted estimates will be interpreted as evidence regarding the extent to which any observed benefit is attributable to personalization of the stimulus rather than to differential expectancy or attention. Time to response or remission will be compared between groups using Kaplan–Meier survival curves and the log-rank test. For study 3, the primary analysis will follow an intention-to-treat principle, including all randomized participants according to their assigned group. A supplementary per-protocol analysis will include only participants who complete at least 80% of scheduled listening sessions (ie, a minimum of 45 of 56 daily sessions).

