#### Missing Data

Missing data patterns will be examined and characterized as missing completely at random (MCAR), missing at random (MAR), or missing not at random (MNAR) using Little’s MCAR test and pattern analyses. Under the MAR assumption, multiple imputation by chained equations (MICE) will be used to generate 20 imputed datasets, and results will be pooled using Rubin’s rules. As a sensitivity analysis, last-observation-carried-forward (LOCF) imputation will be applied within the repeated-measures ANOVA framework, in line with our prespecified protocol. Additional sensitivity analyses under MNAR scenarios, including tipping-point analyses, will be conducted to evaluate the robustness of the findings.

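### Participants withdrawn for deterioration fall to MAR imputation in the primary response analysis, so some recorded treatment failures are imputed as responders

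*Protocol article*

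**What the plan says.** Four parts of the protocol article bear on this point.

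- **Concomitant Treatments:** "Participants who require initiation of prohibited treatments owing to clinical deterioration will be withdrawn from the study". The exit is from the study, and the section does not mention later outcome assessments. It does have concomitant treatments and their indication recorded on the case report form.
- **Sample Size Calculation:** "The primary outcome is the response rate at 8 weeks, defined as a reduction of 50% or greater from baseline". Response is defined by the score alone, here and under Primary Outcome Measure. Starting a prohibited treatment is nowhere classed as non-response.
- **Primary Outcome Analysis:** for study 3, "the primary analysis will follow an intention-to-treat principle, including all randomized participants according to their assigned group"; for the response rate, "between-group comparisons will be conducted using chi-square tests, with results reported as risk difference and risk ratio with corresponding 95% CIs".
- **Missing Data:** "Under the MAR assumption, multiple imputation by chained equations (MICE) will be used to generate 20 imputed datasets". Two sensitivity approaches follow: "last-observation-carried-forward (LOCF) imputation will be applied within the repeated-measures ANOVA framework", and then "Additional sensitivity analyses under MNAR scenarios, including tipping-point analyses, will be conducted to evaluate the robustness of the findings". None of the three is tied to the reason for withdrawal.

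**The concern.** A participant who worsens enough to need a prohibited treatment has failed clinically on the assigned music therapy, and the case report form shows it. The intention-to-treat rule still requires a week-8 value for that person, and the only method given for the main analysis is MAR imputation. An imputed score can fall below half of baseline, and that person then counts as a responder.

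The fault lies in the question being answered. MAR imputation estimates what would have been seen at week 8 had the prohibited treatment not been started. The article neither states nor defends that target, and it fits poorly with an intention-to-treat comparison of response rates.

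At stake is the pooled contrast, which the section on heterogeneity and multiple comparisons calls the confirmatory primary one and whose estimates are meant to plan a definitive trial. Both arms' response rates rise. If deterioration is more frequent in one arm, the difference between arms shifts as well.

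**Working it through.** **The plan's own figure.** The only sample-size figure is a half-width of about 8 to 12 points with 50 per arm, 70% control response and differences of 0 to 30 points. Half-width = z × √[p_C(1−p_C)/50 + p_I(1−p_I)/50]. With z = 1.282 this runs from 11.7 to 8.3 points, which reproduces it as a 2-sided 80% interval. With z = 0.842, the 1-sided 80% label as written, it runs from 7.7 to 5.5. The present point does not depend on this figure.

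**Inputs.** From the protocol: control response 70%, differences of 0 to 30 points, 50 per arm per diagnosis (150 per arm pooled), importance threshold 20 points. Assumed: the share withdrawn for deterioration, w, because the protocol gives none; and response among those who stay, r, of 70% (control) and 80% (IMT).

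**Formula.** Arm rate = (1−w)·r + w·q, where q is the response probability given to those withdrawn. Non-response counting sets q = 0. The extreme MAR case sets q = r, so the arms stay at 70% and 80% and the difference at 10.0 points. Inflation per arm is then w·r: 0.05 × 0.70 = 3.5 points, or 0.10 × 0.70 = 7.0 points. The difference shifts by w_I·r_I − w_C·r_C.

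| w control / IMT | Rates with q = 0 | Difference, q = 0 | Difference, q = r | Shift |
|---|---|---|---|---|
| 5% / 5% | 66.5% / 76.0% | 9.5 | 10.0 | +0.5 |
| 10% / 10% | 63.0% / 72.0% | 9.0 | 10.0 | +1.0 |
| 10% / 5% | 63.0% / 76.0% | 13.0 | 10.0 | −3.0 |
| 15% / 5% | 59.5% / 76.0% | 16.5 | 10.0 | −6.5 |
| 5% / 10% | 66.5% / 72.0% | 5.5 | 10.0 | +4.5 |
| 5% / 15% | 66.5% / 68.0% | 1.5 | 10.0 | +8.5 |

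With a milder q = 0.3 in both arms, the 5% / 15% case gives 4.5 points, a shift of 3.0 from 1.5.

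**Simulation using intermediate visits.** One arm of 200,000 was simulated with assumed score trajectories. Participants were withdrawn at the first of weeks 1, 2, 4 or 6 with a score above 115% of baseline. Missing scores were imputed sequentially by regression on baseline and earlier visits, and response was then derived.

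| Deteriorated score recorded? | Withdrawn | Completers responding | Withdrawn imputed as responders | Arm rate, MAR | Arm rate, non-response | Inflation |
|---|---|---|---|---|---|---|
| Yes | 7.1% | 52.5% | 11.5% | 49.6% | 48.8% | 0.8 |
| Yes | 4.0% | 69.7% | 25.0% | 67.9% | 66.9% | 1.0 |
| Yes | 3.1% | 77.0% | 33.9% | 75.6% | 74.6% | 1.0 |
| No | 7.2% | 52.8% | 40.8% | 52.0% | 49.0% | 3.0 |
| No | 4.0% | 69.7% | 60.1% | 69.3% | 66.9% | 2.4 |
| No | 3.1% | 76.6% | 67.7% | 76.3% | 74.2% | 2.1 |

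The imputed response probability falls below the completers' rate in every row, well below it when the deteriorated score was recorded, but never to zero.

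**The case against.** The strongest reply is that no sentence sends these participants to MICE, and that a statistical analysis plan, to be finalized before database lock, may treat them separately. The link is indeed an inference from three sections. But the article does state a default for missing data, makes no exception to it, and offers nothing else for the main analysis. Followed as written, it gives the result described.

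Second, a reader might infer that this missingness must be not at random because the outcome causes it. The documents do not support that. If worsening is recorded at a visit before withdrawal, missingness depends on observed scores and MAR can hold. Nor is the imputation model confined to people who stayed well; it can use the withdrawn participants' own earlier scores. The objection to the plan is about the estimand.

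Third, a reader might extend the point to other analyses. The article names Kaplan–Meier curves and the log-rank test but gives no censoring rule, so it cannot be said to censor these participants. It also gives no missing-outcome rule for the prediction model.

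Fourth, the sensitivity analyses do probe the issue. Tipping-point analysis is a standard check, and LOCF would carry a recorded poor score forward. But LOCF is placed in an analysis of continuous scores, the MNAR scenarios are not tied to withdrawal reason, and neither changes the primary estimate.

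Finally, study 3 is a pilot. At 70% vs 80% with 150 per arm the 95% half-width is about 9.7 points, so the smaller shifts lie well inside sampling error. That limits the urgency, but bias does not average out as sampling error does.

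**Conclusion.** The point holds as a badly fixed primary-analysis rule: the stated sections together impute some recorded treatment failures as week-8 responders.

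Its size is conditional, because the protocol gives no withdrawal rate. With 3 to 7% withdrawn and assumed trajectories, an arm's response rate is inflated by about 1 to 3 points. The ceiling is w·r, reached if those withdrawn are imputed at the completers' rate. In that extreme case the between-arm difference moves by 0.5 to 1 point under balanced withdrawal. It moves by 3 to 8.5 points, in either direction, under a 5 to 10 point imbalance.

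A reader might reach for a more dramatic example. With true response of 70% vs 80% and 15% vs 5% withdrawn, dividing by those remaining gives 0.70/0.85 = 82.4% and 0.80/0.95 = 84.2%, so 10 points shrink to 1.9. That is a complete-case illustration on assumed withdrawal rates. It uses no intermediate scores and is not what MICE would be expected to return.

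**What to change.** Leave the clinical withdrawal rule unchanged and amend the analysis wording:

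1. In the primary response-rate analysis, count withdrawal for deterioration, or the start of prohibited treatment, as non-response, and state this as the estimand.
2. Restrict MICE to other missing data. Impute the scores by arm and diagnosis, then derive response.
3. If time to response is analysed, treat these participants consistently, as not having responded through week 8.
4. For a supporting analysis, reconcile Concomitant Treatments with the intention-to-treat aim by stating whether already scheduled outcome assessments continue, with consent, after study treatment ends. Scores so collected would not enter the analysis in item 1.

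Items 1 to 3 cost only wording and slightly lower reported response rates, since the case report form already captures the reason. Item 4 asks for a statement; if assessments do continue, the cost is visits already scheduled. It should be settled early, because outcomes not collected cannot be recovered later.

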### Sample Size Calculation

Study 3 is a pilot RCT designed to assess feasibility and to generate preliminary effect estimates to inform a definitive future trial. Accordingly, the sample size is based on precision estimation rather than formal power calculation. The primary outcome is the response rate at 8 weeks, defined as a reduction of 50% or greater from baseline in the disorder-specific symptom severity score. We adopted a minimal clinically important difference–anchored CI approach, setting a 20-percentage-point absolute difference in response rates as the threshold for clinical importance. With 50 participants per arm within each diagnostic group, the expected 1-sided 80% CI half-width for the between-group difference in response rates is approximately 8 to 12 percentage points (derived from a response rate of 70% for the control group and a range of between-group differences from 0% to 30%), thereby permitting precise estimation of feasibility metrics and preliminary efficacy signals to plan the definitive trial.

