#### Heterogeneity of Target Disorders, Subgroup Analyses, and Multiple Comparisons

Recognizing that MDD, GAD, and PI differ in symptom profiles and neurobiological mechanisms, the primary analysis of study 3 will pool all 3 disorders to maximize statistical power, with diagnostic group included as a stratification factor in the randomization and as a covariate in all pooled models. Treatment × diagnosis interaction terms will be included in the mixed-effects models to assess whether treatment effects vary by disorder. If significant heterogeneity is detected, disorder-specific results will be reported separately. The analytic hierarchy is specified a priori as follows. The pooled treatment effect (IMT vs nonindividualized therapy), adjusted for diagnosis, is the confirmatory primary contrast. Disorder-specific treatment effects (MDD, GAD, and PI analyzed separately) are prespecified secondary, hypothesis-generating analyses. For each disorder, we will report the response-rate difference and the MMRM-derived between-group difference in symptom change with 95% confidence intervals, regardless of statistical significance, so that the direction and precision of the per-disorder estimates are transparent and can inform the design of a future definitive trial. The treatment × diagnosis interaction will be evaluated primarily as a test of effect-modification rather than as a gatekeeper for reporting; disorder-specific estimates will be presented whether or not the interaction term reaches significance, but will be explicitly labeled exploratory. We acknowledge that this pilot is not powered for confirmatory subgroup inference. With approximately 50 participants per arm per disorder (100 per diagnostic group), each disorder-specific contrast has limited power to detect between-arm differences smaller than a large effect, and the trial is powered for precision of estimation rather than for hypothesis testing within subgroups (see Sample Size Calculation). To avoid over-interpreting unstable subgroup estimates, the disorder-specific analyses will be supplemented by a hierarchical Bayesian model in which disorder-specific treatment effects are treated as exchangeable and shrunk toward the overall pooled effect; this borrows strength across the 3 disorders and yields more stable, less extreme per-disorder estimates than fully separate analyses. Posterior means and 95% credible intervals for each disorder will be reported alongside the frequentist estimates. We will not draw definitive efficacy conclusions for any individual disorder from study 3; rather, the per-disorder estimates will be used to generate hypotheses and to inform stratified sample-size planning for the definitive trial. It should be noted that the music therapy protocol uses the same affective trajectory for participants with MDD and GAD, whereas a distinct biphasic trajectory is used for participants with PI. This difference in trajectory design reflects the distinct clinical objectives for each disorder and will be accounted for in the analysis by including trajectory type as a covariate in sensitivity analyses. Because trajectory type is collinear with the PI-versus-(MDD and GAD) distinction, this covariate adjustment will be reported as a sensitivity analysis complementary to the disorder-stratified analyses above. For the family of disorder-specific secondary contrasts, the false discovery rate will be controlled using the Benjamini–Hochberg procedure, and both adjusted and unadjusted *P* values will be reported.

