Several limitations should also be noted. First, the open-label design of study 2 precludes causal attribution of observed improvements to the intervention, as natural symptom fluctuation and regression to the mean cannot be excluded in the absence of a control group. However, this limitation is mitigated by the inclusion of a randomized controlled comparison in study 3. Second, complete participant blinding in the RCT is not feasible owing to the inherent differences between the 2 intervention arms, which may introduce differential expectancy effects; moreover, the weekly preference assessment in the IMT arm provides additional participant–researcher contact, engagement, and a sense of agency that is absent from the nonindividualized arm, so that any observed superiority of IMT could in principle reflect this added attention and engagement (a cointervention and attention effect) rather than personalization of the musical stimulus per se. To address these concerns, we have implemented several strategies to minimize bias, as described in the Randomization and Blinding section, including an attention-matched weekly questionnaire in the nonindividualized arm, baseline measurement of treatment credibility and expectancy with expectancy-adjusted sensitivity analyses, and a formal blinding-integrity (bang blinding index) assessment. We nonetheless recognize that these measures reduce, but cannot fully eliminate, the confounding of personalization with attention and expectancy; cleanly separating these components would require designs such as a 3-arm trial incorporating an attention-matched sham-personalization control, which we identify as an important direction for the definitive trial. Third, the pilot RCT is powered for precision of estimation rather than confirmatory hypothesis testing; consequently, the study may be underpowered to detect clinically meaningful differences within individual diagnostic subgroups, and subgroup analyses should be interpreted as exploratory. Because MDD, GAD, and PI differ in symptom profiles, neurobiology, and even in the affective trajectory of the intervention delivered, pooling them maximizes power for the overall comparison but cannot resolve whether the 3 disorders respond differently to IMT; we have therefore prespecified disorder-stratified estimation, a treatment × diagnosis interaction test, and a hierarchical Bayesian model that shrinks per-disorder estimates toward the pooled effect, and we explicitly refrain from drawing disorder-specific efficacy conclusions from this pilot. Definitive, disorder-specific inference will require an adequately powered, stratified trial. Fourth, all studies conclude at 8 weeks, and the durability of treatment effects beyond the intervention period remains unknown. Finally, although EEG offers excellent temporal resolution for capturing dynamic neural responses to music, it provides limited spatial resolution compared with functional MRI, which may constrain the ability to localize treatment-related changes in deep brain structures; in addition, the EEG analyses are exploratory and not powered for confirmatory neurophysiological inference, particularly at the level of individual disorders.

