
### Future Directions

If the pilot RCT demonstrates promising results, a fully powered, multicenter definitive trial will be warranted to confirm the efficacy of IMT across diverse clinical populations. To disentangle the personalization effect from the additional attention and engagement inherent in the IMT procedure, the definitive trial should consider a 3-arm design that adds an attention-matched sham-personalization control (in which participants complete weekly preference ratings but receive nonindividualized music), enabling the specific contribution of stimulus personalization to be isolated. Future studies should also incorporate longer follow-up periods (eg, 12 to 24 wk) to assess the durability of therapeutic effects and the potential for relapse prevention. Adequately powered, diagnosis-stratified samples will be required to draw firm disorder-specific conclusions for MDD, GAD, and PI, and to support confirmatory neurophysiological inference. The prediction model developed in study 4, if validated, could serve as a clinical decision-support tool for identifying patients most likely to benefit from individualized interventions; further refinement using machine-learning approaches with larger datasets would enhance its generalizability. Additionally, the integration of multimodal neuroimaging (combining EEG with fMRI or fNIRS) in future protocols could provide a more comprehensive understanding of the neural circuits engaged by IMT. Finally, investigating the applicability of the IMT framework to other psychiatric conditions, as well as to pediatric and geriatric populations, represents an important direction for extending the reach of this approach.

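### Study 3's pooled comparison is labelled confirmatory although the protocol describes and sizes the trial as a non-confirmatory pilot, and its 20-point threshold never enters the analysis

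*Protocol article*

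**What the plan says.** **Purpose and sizing** (Sample Size Calculation). Study 3 is a pilot for feasibility and preliminary effect estimates, and "the sample size is based on precision estimation rather than formal power calculation". The approach is anchored to a minimal clinically important difference, "setting a 20-percentage-point absolute difference in response rates as the threshold for clinical importance". The precision figure is worked out for a single diagnosis, at 50 per arm. On that basis the protocol says that "the expected 1-sided 80% CI half-width for the between-group difference in response rates is approximately 8 to 12 percentage points". It assumes a 70% control response and differences of 0 to 30 points.

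**Analysis** (Plan for Statistical Analysis; Primary Outcome Analysis). "All hypothesis tests will be 2-sided, with a significance level of" .05. Week-8 response is compared by chi-square test, with the risk difference and risk ratio given with 95% CIs.

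**Status of the pooled contrast** (Heterogeneity of Target Disorders, Subgroup Analyses, and Multiple Comparisons). The primary analysis pools the three disorders. The diagnosis-adjusted pooled effect of individualized versus nonindividualized therapy "is the confirmatory primary contrast". The disorder-specific contrasts are secondary and exploratory.

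**Status of the trial** (Strengths and Limitations). "the pilot RCT is powered for precision of estimation rather than confirmatory hypothesis testing".

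**The concern.** Two things do not fit together.

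First, the current text gives study 3 two statuses. One section makes the pooled comparison confirmatory. Two others describe a pilot that was not sized for a confirmatory test.

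Second, the sizing and the analysis use different standards. The sizing uses a 20-point threshold, an 80% interval and 50 per arm. The analysis uses a null of zero, a two-sided 5% test, 95% intervals and 150 per arm. The threshold and the 80% interval do not reappear, and no precision is stated for the contrast that is actually primary.

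What is at stake is the claim study 3 may support. If the confirmatory label stays, any pooled P value below .05 can be reported as confirmed superiority, including one from a difference well short of what the protocol calls clinically important.

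**Working it through.** **Inputs**
- Control response 70%, differences 0 to 30 points, 50 per arm per diagnosis, threshold 20 points (Sample Size Calculation).
- 300 participants randomized 1:1 (Table 1), so 150 per arm when pooled.
- Two-sided alpha .05, chi-square test, 95% CI (Plan for Statistical Analysis; Primary Outcome Analysis).
- Continuity correction for 2×2 tables is stated under Descriptive and Baseline Analyses. Whether it also applies to the primary test is not said, so both versions are shown.

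**Step 1. The protocol's own precision figure**

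Half-width = z × √[p₁(1−p₁)/n + p₂(1−p₂)/n], with n = 50 and p₁ = 0.70.
- Difference 0: SE = √(0.42/50) = 0.0917.
- Difference 30 points: SE = √(0.21/50) = 0.0648.
- With z = 1.282 (two-sided 80%): 11.8 down to 8.3 points, which reproduces 8 to 12.
- With z = 0.842 (one-sided 80%, as labelled): 7.7 down to 5.5 points, which does not.

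The printed figure is therefore a two-sided 80% half-width. That is a separate labelling matter and nothing below depends on it.

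**Step 2. Where the pooled test becomes significant**

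Take 105/150 (70%) responders in the control arm and raise the count in the other arm. Here z = difference / √[2p̄(1−p̄)/150], and the continuity correction subtracts 1/150 from the difference.

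| Comparison arm | Difference | p̄ | SE | z | p |
|---|---|---|---|---|---|
| 119/150, uncorrected | 9.3 points | 0.747 | 0.0502 | 1.86 | 0.063 |
| 120/150, uncorrected | 10.0 points | 0.750 | 0.0500 | 2.00 | 0.046 |
| 121/150, corrected | 10.7 points | 0.753 | 0.0498 | 0.100/0.0498 = 2.01 | 0.045 |

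Significance starts at 10.0 points, or 10.7 with the correction. If the control rate were 30% to 60% (an assumption), the uncorrected boundary by normal approximation would be 10.8 to 11.3 points.

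**Step 3. What a just-significant result says about 20 points**

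At 120/150 versus 105/150 the unpooled SE is √[(0.21 + 0.16)/150] = 0.0497. The 95% CI is 10.0 ± 9.7, that is 0.3 to 19.7 points. The result is significant, yet the whole interval lies below the protocol's threshold.

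**Step 4. Precision of the contrast that is primary**

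With n = 150 and z = 1.96:
- Difference 0: 1.96 × √(0.42/150) = 1.96 × 0.0529 = 10.4 points.
- Difference 30 points: 1.96 × √(0.21/150) = 1.96 × 0.0374 = 7.3 points.

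The pooled 95% half-width is thus about 7 to 10 points. The protocol gives no such figure for the pooled contrast.

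**The case against.** - **Confirmatory may only be a ranking.** The word stands in an analytic hierarchy and could mean no more than that the pooled contrast outranks the disorder-specific ones. The consequence drawn in Strengths and Limitations also concerns subgroups. This softens the conflict but does not remove it. The opening clause there covers the whole pilot RCT, the Sample Size Calculation says the same, and a reader of the results will take confirmatory in its usual sense.
- **The pooled sample is not small.** At 70% versus 90% with 150 per arm, power is Φ[(0.200 − 1.96 × 0.0462)/0.0447] = Φ(2.45), about 99%. A confirmatory pooled test could have been planned. The protocol did not do so: it expressly declines a power calculation and states precision only per diagnosis.
- **Significance and clinical importance are different questions.** A significant effect below the important difference is an ordinary result. That is correct, and such a result alone is no contradiction. The defect is that it would carry a confirmatory label while the threshold set at the design stage plays no part in reading it.
- **A stronger reading is tempting.** A reader might infer two competing decision rules, under which a definite band of pooled differences succeeds by the 5% test and fails by the 20-point standard. The protocol does not support this. It never says whether an upper limit, a lower limit or the point estimate is to be set against 20. At 150 per arm and a 70% control rate, the upper end of such a band would be 13.9 points (two-sided 80% upper limit reaching 20), 16.1 (one-sided 80% upper limit), 20 (point estimate), 23.6 (one-sided 80% lower limit) or 25.3 (two-sided 80% lower limit). Nor does any passage tie a verdict on the trial to P below .05.
- **Progression criteria.** Future Directions says "If the pilot RCT demonstrates promising results, a fully powered, multicenter definitive trial will be warranted" without defining promising. That is a discussion sentence, and such criteria may properly sit in the full protocol or SAP. Their absence here is not counted as a fault.

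**Conclusion.** The concern holds as an internal contradiction on status together with an unlinked threshold. The pooled contrast is called confirmatory in one section, while two others say that study 3 was not sized for confirmatory testing. The 20-point threshold and the 80% interval do not carry through to the analysis.

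On the protocol's 70% control rate, with 150 per arm and complete data, the pooled test is significant from 10 points (10.7 continuity-corrected), about half the stated threshold. The calculation uses the simple chi-square test and Wald limits without adjustment for diagnosis, so adjusted results may shift slightly.

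It does not follow that the protocol holds two incompatible success rules, that a specific range of results flips the verdict, or that a go decision is fixed wrongly, because no such rules are written. The disorder-specific contrasts are already labelled exploratory and raise no issue here.

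**What to change.** 1. In the section on heterogeneity of target disorders, replace the confirmatory label with *primary estimate*, or *primary contrast, not confirmatory*. This agrees with Sample Size Calculation and Strengths and Limitations.
2. In Primary Outcome Analysis, report the pooled, diagnosis-adjusted week-8 risk difference with its two-sided 95% CI, interpret it explicitly against the 20-point threshold, and state that the P value is supportive.
3. In Sample Size Calculation, add the expected precision of the pooled contrast: a 95% half-width of about 7 to 10 points at 150 per arm, for a 70% control response and differences of 0 to 30 points.

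The cost is wording in the protocol and the SAP, with no change to sample size or procedures. The downside is that a significant P value from study 3 can no longer be presented as confirmatory.
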